# Use of virtual reality to remotely train healthcare professionals in paediatric emergency tracheostomy skills: protocol for a multi-centre, non-inferiority educational interventional study with historical controls

**DOI:** 10.1186/s12893-024-02736-1

**Published:** 2025-01-15

**Keywords:** Virtual reality, Simulation training, Tracheostomy, Paediatrics

## Abstract

**Background:**

The insertion of a tracheostomy is an established technique used to wean patients off ventilatory support, manage secretions in complex conditions, and as a potentially life-saving procedure to bypass upper airway obstruction. Life-threatening complications during aftercare are not uncommon and may be influenced by a lack of education of carers or healthcare providers of children and young people living with a tracheostomy. Education programmes designed and supported by the National Tracheostomy Safety Project are effective, but resources are not available to educate the workforce at scale. With the overarching aim of widening access to paediatric tracheostomy skills training, we present the protocol for the development and evaluation of a novel virtual reality (VR) training tool designed to simulate the emergency management of paediatric tracheostomy complications.

**Methods and discussion:**

A multi-centre, non-inferiority educational interventional study with historical controls will be used to evaluate the novel VR training package. A group of 69 healthcare staff and students will have one week to use the educational intervention as often as necessary to learn paediatric emergency tracheostomy skills. The primary outcome measure is skill performance in simulation in a pre- and post-intervention structure within subjects. Participant performance will also be assessed using non-inferiority metrics against historical traditional educational control data. Secondary outcomes include knowledge gain, knowledge retention, usability, side effects, and participant satisfaction. To minimise the risk of cybersickness, teleportation was the preferred locomotion method for the user navigation within the VR environment.

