### Overall aim and research questions

The novel VR tracheostomy training package will be used as described in Table 1. By evaluating this novel VR training package, we aim to explore whether healthcare students can gain knowledge and skills relevant to managing paediatric tracheostomy emergencies using immersive technology in their homes. In addition to skill acquisition and knowledge, we aim to understand the usability of these devices in the remote setting and learn about the user's satisfaction levels and perception of realism by utilising the training package in a self-directed manner. The research questions are as follows:Is fully remote, unsupervised VR training non-inferior to traditional training?Do participants enjoy and feel they can learn from fully remote VR training?

**Table 1 Tab1:** Summary of the VR educational activity

Activity	Detail
**Onboarding (5 min)**	This 5-min experience guides the participant through using the controllers to interact with the environment and virtual objects and move around. It teaches the user how to perform specific interactions, such as suctioning the tracheostomy and speaking to the avatar in the simulation
**History taking (5–10 min)**	The user is expected to take a brief history from a simulated avatar of the patient’s mother as they have attended the emergency department due to a cough and fever. The user will be able to ask relevant questions verbally and be responded to by the avatar. The aim is to gather any information regarding when the tracheostomy was inserted, when the tracheostomy was last suctioned, any allergies the patient may have, and whether the patient has eaten before coming to the hospital. This is to determine whether the procedure can go forth
**Algorithm tutorial training (5–10 min)**	This is a guided tutorial that demonstrates and allows the user to practice using the emergency tracheostomy algorithm. It introduces the blue emergency box, algorithm card, and equipment required to complete the process of decannulating the child. There are no elements of stress in this scene; it is purely a learning space
**Algorithm simulation assessment (5–10 min)**	This section will expose the user to an emergency and require them to progress through the blocked tracheostomy algorithm Feedback is given to the user around time, including interventions they have completed and ones they missed The user can repeat the assessment or the tutorial to improve their time

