### Statistical calculations

Sample size calculations were performed by an MFT statistician (AR) to assess for non-inferiority of VR training compared to the current standard training. In the historical data set, the standard deviation for total scenario time after standard training was 70 s. The non-inferiority margin is assumed to be 30 s. Assuming the expected time to key specific interventions and completion of the scenario for the two groups are the same, the sample size is calculated so that the upper limit of the one-sided confidence interval for the mean difference in time (VR- standard) is below 30 s. A 97.5% one-sided confidence interval for non-inferiority translates to a 95% two-sided confidence interval, provided the upper limit is below 30 s. The calculation provided led to a proposed sample size of 69 participants. Descriptive statistics will be obtained from the pre and post course surveys and the assessment data. Secondly aggregate measures will be constructed for further analysis. Examples of aggregate measures include:Mean values for the simulation performance (primary outcome)Mean values for knowledge test score

The data will be compared to historical data from a course designed to teach the same learning outcomes. Specific measures for performance will be compared, including total scenario completion time and time to specific key interventions.

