### Primary outcome—assessment of performance in simulation

The participants synthesised knowledge will be assessed before and after the intervention during a traditional simulation skills session. Both sessions will include a pre-brief, with the second session following up with a de-brief pedagogical methodology as per best standards in simulation design [14]. The simulation will have the same layout and equipment as the VR training tool. These sessions will be analysed on-site, and the following data will be taken:Overall success in task (measured as a binary ‘yes’ or ‘no’ outcome)Steps completed (all measured as a binary ‘yes’ or ‘no’ for each of the below individual steps marked a-g)Call for helpLook / listen / feelApply oxygen – faceApply oxygen – tracheostomyRemove any attachmentsAttempt suctionRemove tracheostomyTime to key interventions (measured in seconds for all individual steps below marked a-c)Apply oxygen to face and neckCall for helpCompletion of simulation

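### The declared primary outcome is a within-subject pre/post comparison, but the title, design, first research question and sample size all rest on non-inferiority to historical training

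*Protocol article*

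**What the plan says.** The abstract (Methods and discussion) states: "The primary outcome measure is skill performance in simulation in a pre- and post-intervention structure within subjects". Its next sentence reads: "Participant performance will also be assessed using non-inferiority metrics against historical traditional educational control data".

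Other sections place the weight elsewhere:

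- The title describes a "protocol for a multi-centre, non-inferiority educational interventional study with historical controls". The opening of Materials and methods repeats this design.
- The first research question (Overall aim and research questions) asks: "Is fully remote, unsupervised VR training non-inferior to traditional training"?
- Statistical calculations says that the sample size was worked out "to assess for non-inferiority of VR training compared to the current standard training". It uses an SD of 70 s for total scenario time, a margin of 30 s, no expected difference between groups, and a 97.5% one-sided bound on VR minus standard that must fall under 30 s. The result is 69 participants.

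The section headed Primary outcome returns to the pre/post frame: "The participants synthesised knowledge will be assessed before and after the intervention during a traditional simulation skills session". It then lists one overall success item, seven steps ("all measured as a binary ‘yes’ or ‘no’ for each of the below individual steps marked a-g") and three times in seconds. None is ranked above the others. Statistical calculations attaches the primary-outcome label to mean simulation performance, given as an example of an aggregate measure. It also says that both completion time and times to key interventions will be compared with the historical data.

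**The concern.** A within-subject change and a difference from historical controls are different estimands with different comparators. The first asks whether participants improve after a week with the VR package. The second asks whether they end up no worse, by more than 30 s, than people trained in the usual way. An improvement of any size is compatible with being worse than standard training, so a positive pre/post result does not answer the study's own first question.

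What is at stake is which result counts as the conclusion. If the pre/post analysis is positive and the non-inferiority analysis is not, the abstract supports calling the study a success, while the title and sample size support the opposite. The eleven unranked measures leave further room to choose a headline after the data are seen.

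**Working it through.** **1. Statements side by side.**

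| Place | Comparison | Variable |
|---|---|---|
| Abstract, primary outcome | Within subject, pre/post | Skill performance, not specified |
| Abstract, added assessment | VR against historical | Performance, not specified |
| Title; design statement | Non-inferiority, historical controls | None named |
| First research question | Non-inferiority to traditional training | None named |
| Statistical calculations, sizing | VR minus standard, bound under 30 s | SD is for total scenario time; the no-difference assumption also covers key-intervention times |
| Primary outcome section | Before and after | 1 + 7 + 3 = 11 measures |

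The comparison labelled primary is not the one that defines the design or the size.

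**2. What 69 was sized for.** Inputs from Statistical calculations: SD 70 s, margin 30 s, true difference 0, one-sided 0.025. Power and the number of controls are not given, so 69 cannot be reproduced uniquely. For equal groups, n = 2 × [SD × (z for alpha + z for power) / margin]².

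- One-sided 0.025, 80% power: 2 × [70 × (1.960 + 0.842)/30]² = 85.5, so 86 per group.
- One-sided 0.05, 80% power: 2 × [70 × (1.645 + 0.842)/30]² = 67.3, so 68 (69 with the t distribution). This matches 69 but not the stated 97.5% level.
- Historical mean taken as fixed, one-sided 0.025, 95% power: [70 × (1.960 + 1.645)/30]² = 70.8, so 71.

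None of these routes uses a pre/post quantity. The article states no target change, SD of change or within-subject correlation.

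**3. Power for non-inferiority of total time with 69 VR participants.** SE = 70 × √(1/69 + 1/m), where m is the number of controls (assumed). Power = Φ(30/SE − 1.96).

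| m | SE (s) | Power |
|---|---|---|
| 30 | 15.3 | 0.50 |
| 69 | 11.9 | 0.71 |
| 112 | 10.7 | 0.80 |
| 200 | 9.8 | 0.87 |
| historical mean fixed | 8.4 | about 0.95 |

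**4. What 69 pairs could detect pre/post.** Assume SD 70 s at both visits, two-sided 0.05 and 80% power. The detectable change is 0.342 × 70 × √(2(1 − ρ)).

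- ρ = 0: 33.9 s
- ρ = 0.5: 23.9 s
- ρ = 0.7: 18.6 s

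These values of ρ are assumptions. The range shows only that the two analyses answer to different quantities and can disagree.

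**5. The 30 s rule on more than one time.** Suppose it were applied to all three times at one-sided 0.025, each with a true difference at the margin. With independence, the chance of at least one false claim is 1 − 0.975³ = 0.073. The times come from one scenario and are probably positively correlated, so 0.073 is an upper-end figure.

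**The case against.** The strongest reply is that there is one outcome domain, simulation performance, with two planned comparisons. The same abstract paragraph opens by calling this a non-inferiority study. Description of the intervention says the assessment measures are the same as in the historical study and are what the statistical comparisons rest on. A separate analysis plan may rank the analyses and deal with multiplicity. Part of this stands: a missing test hierarchy is no finding here. But the article did not leave the primary outcome to another document. It stated it, tied it to the pre/post structure, and added non-inferiority with an "also" sentence: "Participant performance will also be assessed using non-inferiority metrics against historical traditional educational control data". An analysis plan would not remove that conflict with the title and the sizing.

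Several stronger readings are tempting, and the article does not support them.

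- *The title and research question concern total scenario time.* They name no endpoint. Only Statistical calculations uses total time.
- *There is no decision rule at all.* There is one, the bound under 30 s. The defect is that it is not designated primary or tied to a single time.
- *Eleven tests at 2.5% give a 24% false-claim rate* (1 − 0.975¹¹ = 0.243). No margin or test is stated for the eight yes/no items, and the plan speaks of descriptive and aggregate measures. The three-time figure is the one closest to the text.
- *Power for non-inferiority is 71%.* That holds only with 69 controls, a number the article does not give.
- *A pre/post gain is practically certain.* No figure supports this, and the second scenario differs from the first in its clinical details. The point does not need it.

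**Conclusion.** The concern holds as an inconsistency in stated text. The declared primary comparison cannot answer the first research question and has no stated sample-size basis. The comparison that does have one is described as additional, and its criterion is not attached to one variable. The study could therefore meet its declared primary and miss its titular question, with nothing in the article to say which result prevails.

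This conclusion rests on the wording alone and does not depend on whether 69 can be reproduced. The figures only illustrate its size. The error rate of up to about 7% assumes the 30 s rule is read on all three times and that they are independent. The power of 0.50 to about 0.95 assumes the stated SD, margin and one-sided 0.025, and spans 30 controls up to a historical mean treated as known. The wording should be settled before the data are analysed, because it fixes what the study can conclude.

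**What to change.** In the abstract, Statistical calculations and the Primary outcome section, name the same single primary variable and comparison. The one that fits the existing sizing is total scenario completion time at the post-training simulation, VR minus historical, with non-inferiority concluded if the upper limit of the two-sided 95% interval is below 30 s. Reword the abstract so that this comparison is no longer an addition.

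Make the within-subject pre/post change in total time a key secondary. Label overall success, the seven steps and the two other times as supportive, reported with intervals and without a non-inferiority claim. The authors could choose another primary, but it would then need its own margin or target change and its own sizing.

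The cost is wording only, with no new data. The downside is that fewer measures can carry a headline claim.

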**Trial registration:**

Full registration of this study was completed at ClinicalTrials.gov. The registration number is NCT06350708 and was accepted on the 4th April 2024.

**Supplementary Information:**

The online version contains supplementary material available at 10.1186/s12893-024-02736-1.

## Introduction

The emergency management of the paediatric tracheostomy represents a critical intervention for children and young people (CYP) living with a tracheostomy [1]. Comprehensive training is indispensable to ensure this vulnerable group's safe and effective care. However, traditional tracheostomy education currently available online, involves limited access to practical training opportunities. Therefore, the healthcare workforce, both in the community and in secondary care, relies heavily on in-person teaching methods [2]. This approach poses logistical challenges and can carry cost and environmental impact considerations due to trainer and trainee travel, equipment, and disposable single-use use consumables [3].

In recent years, virtual reality (VR) technology has emerged as a promising tool for healthcare training, offering potentially immersive and realistic simulations that can replicate sometimes complex emergency scenarios [4–6]. In this protocol, we present the planned testing of a state-of-the-art paediatric VR tracheostomy training tool designed to provide students with limitlessly repayable education while enabling remote assessment of their knowledge acquisition.

The primary aim of this study is to examine the effectiveness of the VR paediatric tracheostomy training tool in facilitating learning and enhancing students’ understanding of the emergency management protocol as described by the National Tracheostomy Safety Project (NTSP) (www.tracheostomy.org) [7]. The NTSP blocked tracheostomy protocol is the current 'gold standard' management algorithm taught in UK hospitals using traditional mannequin-based simulation [7]. By providing a safe and controlled virtual environment, we aim to enable learners to engage in hands-on practice, hone their practical emergency algorithm skills, and gain confidence in caring for CYP living with a tracheostomy. Academics and institutions have been exploring VR as a medical education tool over the past two decades [8]. Despite the dramatic increase in consumer use, implementation in the UK healthcare system is limited, with several contributing factors including lack of understanding, confusion in the literature around terminology, the likelihood of cybersickness and no standard way of distributing education using these technologies [8]. Several options exist, including using VR as part of medical courses, using VR on-site in physical settings such as hospitals, universities, or another educational setting, or fully-remote deployments that allow learners to engage with VR content from home or location via online platforms [9]. Additionally, the NTSP have developed a VR course to train in adult tracheostomy safety skills in a supervised remote model [10]. Distance learning has the advantage of liberating trainers and not requiring specialised spaces within healthcare settings. However, the learner cannot utilise the value of real-time educator-student interaction. This article contributes to the growing body of research on distance based VR education in healthcare. By testing the effectiveness of a novel paediatric VR tracheostomy training tool, we aim to explore the acceptability and educational equivalence of VR versus traditional simulation training for the acquisition of knowledge and skills required to manage the paediatric tracheostomy emergency.

### Overall aim and research questions

The novel VR tracheostomy training package will be used as described in Table 1. By evaluating this novel VR training package, we aim to explore whether healthcare students can gain knowledge and skills relevant to managing paediatric tracheostomy emergencies using immersive technology in their homes. In addition to skill acquisition and knowledge, we aim to understand the usability of these devices in the remote setting and learn about the user's satisfaction levels and perception of realism by utilising the training package in a self-directed manner. The research questions are as follows:Is fully remote, unsupervised VR training non-inferior to traditional training?Do participants enjoy and feel they can learn from fully remote VR training?

**Table 1 Tab1:** Summary of the VR educational activity

Activity	Detail
**Onboarding (5 min)**	This 5-min experience guides the participant through using the controllers to interact with the environment and virtual objects and move around. It teaches the user how to perform specific interactions, such as suctioning the tracheostomy and speaking to the avatar in the simulation
**History taking (5–10 min)**	The user is expected to take a brief history from a simulated avatar of the patient’s mother as they have attended the emergency department due to a cough and fever. The user will be able to ask relevant questions verbally and be responded to by the avatar. The aim is to gather any information regarding when the tracheostomy was inserted, when the tracheostomy was last suctioned, any allergies the patient may have, and whether the patient has eaten before coming to the hospital. This is to determine whether the procedure can go forth
**Algorithm tutorial training (5–10 min)**	This is a guided tutorial that demonstrates and allows the user to practice using the emergency tracheostomy algorithm. It introduces the blue emergency box, algorithm card, and equipment required to complete the process of decannulating the child. There are no elements of stress in this scene; it is purely a learning space
**Algorithm simulation assessment (5–10 min)**	This section will expose the user to an emergency and require them to progress through the blocked tracheostomy algorithm Feedback is given to the user around time, including interventions they have completed and ones they missed The user can repeat the assessment or the tutorial to improve their time

## Materials and methods

The planned study is a multi-centre non-inferiority educational interventional study with historical controls. Historical control participants undertook a simulation course designed to train individuals in caring for the paediatric tracheostomy patient, which was run by the Paediatric Working Group of the NTSP (www.tracheostomy.org). This data set was published as a scientific abstract in 2015 in the British Journal of Anaesthesia and was available to the study management group [11]. The educational intervention will provide access to a remote, unsupervised VR training package designed to teach the management of the paediatric tracheostomy emergency using a nationally established emergency algorithm.

The VR training package has four key sections in which the user must complete:Onboarding Section: This section provides instruction on how to navigate the virtual environment familiarising the user with the controls and interactions used within the simulation.History-Taking Section: Prior to proceeding with the main simulation**.** Users engage in a verbal conversation with an AI avatar to ask relevant questions and gather relevant information regarding the tracheostomy.Algorithm Tutorial Section: This section is a step-by-step guide aligned with the national algorithm card. Each step and interaction are explained and highlighted in the correct sequence, allowing the user to acquaint themselves with the process.Algorithm Simulation Assessment: This section exposes the user to an emergency scenario with added triggers to simulate high pressure conditions. The user is expected to perform the correct sequence of steps without assistive prompts within a certain timeframe, this allows them to practice critical decision-making. Once they have completed the assessment, detailed feedback is provided including the number and sequence of steps performed along with the time taken. Users can identify areas of improvement and repeat the algorithm tutorial and assessment section until they feel competent for real-life scenarios.

To minimise the risk of cybersickness, teleportation was the preferred locomotion method for the user navigation within the VR environment [12]. Traditional VR movement options such as joystick-based locomotion can cause discomfort and disorientation due to mismatched sensory feedback. Teleportation on the other hand, allows the user to snap from one point to another reducing the likelihood of nausea and dizziness. Additionally, teleportation contributed to the performance of the simulation by keeping the frames per second (FPS) at a steady 72, which is a crucial factor when creating smooth and responsive experiences. Higher FPS ensures the virtual environment, interactive objects and animations are rendered smoothly, reducing lag that could negatively impact user experience and immersion.

